### Sample size calculations

The required sample sizes for each primary outcome were determined using simulation to incorporate the clustering (table 1) and to take the baseline and end-line surveys into account. Briefly, we simulated 1000 trials with variation between them caused by drawing different samples from the same distributions. We then used the regression models detailed in the data section to analyse each of the simulated trials and estimate the power as the proportion of trials which detected the effect of the intervention as significant. The simulation code was written in R (online supplemental files 2 and 3).

10.1136/bmjopen-2021-051823.supp2Supplementary data

10.1136/bmjopen-2021-051823.supp3Supplementary data

For each country, we require the probability of α, a type I error (rejecting the null hypothesis when it is actually true) to be less 0.05 and the power to be at least 80%.

For vaccination adherence, using a sample size of 35 HF per arm, we would have 80% power in each country to detect as significant a difference between a proportion of due vaccines given from 75% in the control to 85% in the intervention arms, assuming one child per household, 30 households per HF and a between-HF variation equivalent to a k of 0.25, where k is equal to the SD divided by the mean. The value of k is unknown, but was chosen in line with general observations by Hayes and Bennett.^20^

For data quality outcomes, with 35 HF per arm we would be able to detect as significant a difference from a ratio of 0.7 (reported:recorded) vaccinations in the control arm to 0.8 with the intervention with 80% power, assuming 100 recorded vaccinations per HF and an SD of 0.25 in the ratios between HF.

In terms of diagnostic scope, we would be able to detect an increase in the proportion of child visits with more than one diagnosis from 30% to 35% with 80% power with 35 HF per arm, 60 records per HF and assuming a k of 0.25.

We would be able to detect as significant an increase from 50% of treatments having a corresponding appropriate diagnosis to 60% with 80% power assuming 35 HF per arm, 1 treatment per child, 25 children per HF and variation between HF corresponding to k=0.25.

For the outcome related to HWs’ satisfaction, we would be able to detect as significant an increase from 50% of HWs satisfied to 75%, with 80% power assuming 35 HF, three HWs per HF and a variation between HF equivalent to k=0.25. Since this variable is measured in the end-line survey only, we used the formula in Hayes and Bennett.^20^

In summary, in each country we require 35 HF per arm, 3 HW per HF, 100 vaccination records per HF, 60 sick child records per health facility and 30 children per health facility catchment area.

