### Allocation and blinding

Allocation of HF into the intervention and control arms took place in a formal event, gathering research partners and MOH officials to offer transparency and promote study ownership by local and national authorities. Equally sized, folded pieces of paper with the names and codes of included HF written on them were introduced in an opaque receptacle where they were manually and blindly mixed. A second receptacle contained two equally sized pieces of paper, one with the word ‘intervention’ and another one with the word ‘control’. A selected person in the meeting, not belonging to the research team, extracted one piece of paper at a time to reach half the number of included HF. Then, a paper was extracted from the second receptacle to assign those HF to the intervention or control arms. The rest of the papers were extracted as well to verify completeness and no duplication of names, and those HF were assigned to the other arm.

Once HFs were selected, all villages or settlements for each health facility catchment area were listed and three in each catchment area were selected. In practice, we selected all villages because the numbers were below (in Côte d’Ivoire) or just above (in Nigeria) the needs. For each village, we used Google satellite maps to identify and geo-locate every visible roof. Where there were many houses per village (roughly, more than fifty or so), a researcher would mark four points in the map slightly beyond the northernmost, southernmost, easternmost and westernmost roofs seen and 30 random points were selected within that square. From the mapped points, 10 per village (with 20 more acting as reserve) were randomly selected and marked on another map used in the field for data collectors to approach households. Where technical problems impeded this approach in a given village, a field supervisor would rotate a bottle on the floor towards the centre of the village and would select at random 10 households in the direction pointed by the bottle, from the outer limit of the village till the centre.^11^

Blinding is only feasible for the research team members carrying out the CRCT data collection and the analyses of the CRCT findings. The intervention (ie, paper tools) are by design very different from the existing system and it is not possible to blind participants or principal researchers.

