### Data analysis

The analysis will be carried out for each country separately, and based on intention to treat.

Baseline population and health facility characteristics (ie, basic demographic characteristics of population and HWs, professional profile of HWs, health facility size and services) will be summarised. If large imbalances are observed at baseline, the variables can be used to adjust the effect estimate comparisons.^29 30^

The analyses vary for the different primary outcomes due to the unit of measurement and levels of clustering, the type of variable, and whether measurements were taken at baseline and endpoint or endpoint only. We use regression models to allow us to estimate the effect of the outcome while flexibly accounting for these issues and allowing adjustment for potential confounders.

Logistic regression will be used for the binary variables: vaccine adherence is measured by determining whether each vaccine due was received, and treatment appropriateness by whether each treatment was correctly prescribed. Data concordance and diagnostic scope are count variables and may be analysed with Poisson regression, depending on their distribution. The regression model for HW satisfaction will depend on how it is distributed.

The outcomes have different levels of clustering (children or consultations, HW, HF). We will account for these levels of clustering by including random effects in the regression models.

Four of the primary outcomes are measured at baseline and end-line. The effect of the intervention will be estimated using an interaction term between arm and survey in the regression models: that is, is the change in the outcome between baseline and follow-up in the intervention arm different to the change between baseline and follow-up in the control arm? The effect of HW satisfaction in Nigeria, measured only at end-line, will be estimated as the difference between the intervention and control arms.

All estimates for the effect of the intervention will be presented with 95% CIs. The analyses will be carried out using R.^31^

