## Ethics and dissemination

Ethics committees in Côte d’Ivoire, Mozambique and Nigeria approved the study in their respective countries. To date, some modifications to the protocol have taken place. In Côte d’Ivoire, we decided to select study areas close to the research institution based on logistics and practical reasons, instead of selecting an area in the north of the country, where poorer health indicators have been described. In Mozambique, the low density of HF per population implied extremely vast distances between HF and this, coupled with the rainy season, made the trial unfeasible in the originally selected Nampula province. After consultations, we decided to move the trial to the province of Inhambane and cancel the household survey. The allocation of HF to the intervention and control arms was completed using random number generation.

We plan to disseminate the findings of the trials as one of the few examples of studies assessing the effects of HISs interventions using experimental study designs.^34^ Most of the experimental studies on HIS are circumscribed to specific healthcare areas (eg, tuberculosis, vaccination, cardiovascular disease) and very few have a system-wide approach (eg, PHC).^34^ Experimental studies for health systems interventions are sometimes dismissed because of their limited capacity to provide reliable explanations of complex health system issues.^35^ While we acknowledge these limitations, there is also a need for more robust evidence on the effects of these types of health system interventions^36^ and there are also good examples of experimental studies reporting findings that can make it to the policy arena.^37^ When embarking on this research, we considered from the outset the type of evidence required to be disseminated and included into systematic reviews,^38^ guidance development^39^ and eventually recommendations for policy and practice.^40^

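### Vaccination adherence is claimed to have 80% power in each country, but Mozambique has no household survey to measure it; in the other two countries the claim assumes an infant in every sampled household

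*Protocol article*

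**What the plan says.** Sample size calculations sets the standard country by country: type I error is "to be less 0.05 and the power to be at least 80"%. For vaccination adherence it then says "we would have 80% power in each country to detect as significant a difference between a proportion of due vaccines given from 75"% to 85%, with 35 health facilities (HF) per arm, "assuming one child per household, 30 households per HF and a between-HF variation equivalent to a k of 0.25". The section's closing summary lists, for each country, "30 children per health facility catchment area".

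Table 2 gives the subjects as children under 1 year from a sample of households in the catchment areas. The Outcomes text also places this measure in a random household sample. No other data source is named.

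Ethics and dissemination reports for Mozambique that "we decided to move the trial to the province of Inhambane and cancel the household survey". The Abstract agrees: household surveys were done in two of the three countries.

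Data analysis says that countries are analysed separately and that "Four of the primary outcomes are measured at baseline and end-line", with no exception for Mozambique. The effect is the arm-by-survey interaction.

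Allocation and blinding describes the household sample: three villages per catchment area, then 10 random mapped points per village with 20 more in reserve. On the villages it adds "In practice, we selected all villages because the numbers were below" the need in Côte d'Ivoire and just above it in Nigeria. It mentions no check that a household has an infant.

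**The concern.** The power and sample-size statements describe three household surveys, and the trial has two. A reader of the methods alone would take vaccination adherence to be a powered primary outcome in Mozambique, where it will not be observed.

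More than wording is at stake. Measures to minimise bias accepts that outcomes drawn from the health information system may be biased, since that system is what the intervention changes, and offers household-level outcomes as the remedy. In Mozambique the four remaining primary outcomes are data concordance, diagnostic scope and treatment appropriateness, all read from facility records that differ between arms by design, and satisfaction among health workers who know their arm. The remedy does not reach that country.

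A second question concerns Côte d'Ivoire and Nigeria. The calculation treats 30 households as 30 children, but the outcome is restricted to infants and the households are drawn at random. If the yield is lower, the information per facility is lower than the calculation assumed.

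**Working it through.** **1. Mozambique, from the text alone.**
- Source of the outcome: the household sample only (Table 2, Outcomes).
- Household survey in Mozambique: cancelled (Ethics and dissemination); two of three countries surveyed (Abstract).
- Unit of analysis and of the power claim: each country (Data analysis, Sample size calculations).

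Children per facility in Mozambique = 0, so the country-specific effect cannot be estimated. Sample size calculations describes satisfaction as measured at end-line only. The four outcomes said to be measured twice are then the other four, including vaccination adherence, so that sentence does not fit Mozambique.

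**2. The stated 80%.** Printed inputs: p0 = 0.75, p1 = 0.85, c = 35 per arm, n = 30, k = 0.25. Two-sided α = 0.05 is my assumption, as sidedness is not printed.

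*End-line only, Hayes-Bennett formula:*
V = (0.75×0.25 + 0.85×0.15)/30 + 0.25²×(0.75² + 0.85²) = 0.0105 + 0.0803 = 0.0908.
Power = Φ(√(34×0.10²/0.0908) − 1.96) = 49%. About 72 facilities per arm would be needed for 80%.

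*Baseline and end-line, difference in changes:*
Var = [0.69×D/n + s×0.25²×2.41]/35, power = Φ(0.10/√Var − 1.96), where
- 0.69 = 3×0.75×0.25 + 0.85×0.15
- 2.41 = 3×0.75² + 0.85²
- s = share of between-facility variance not common to the two surveys (not printed)
- D = 1 for one observation per child, or (1 + 9×0.5)/10 = 0.55 for 10 doses with within-child correlation 0.5 (both values assumed).

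At n = 30 and D = 1, power is 97%, 86%, 73%, 67%, 47% and 30% for s = 0, 0.10, 0.20, 0.25, 0.50 and 1. The stated 80% lies inside this range. The printed inputs neither confirm nor refute it, because the simulation code is in supplements not shown.

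**3. Infant yield in Côte d'Ivoire and Nigeria.** The share of households with a child under 1 year is not in the article. I assume 15% to 30%.
- 30 households: 30×0.15 = 4.5 to 30×0.30 = 9 infants.
- All 90 mapped points (3×30): 13.5 to 27 infants.
- 30 infants from 90 points needs 30/90, one household in three.

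Power from the formula in step 2:

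| Infants per HF | s = 0, D = 1 | s = 0, D = 0.55 | s = 0.10, D = 1 | s = 0.10, D = 0.55 |
|---|---|---|---|---|
| 4.5 | 33% | 53% | 30% | 47% |
| 9 | 57% | 82% | 50% | 70% |
| 13.5 | 74% | 94% | 63% | 81% |
| 16 | 81% | 97% | 69% | 85% |
| 27 | 96% | 100% | 84% | 93% |
| 30 | 97% | 100% | 86% | 95% |

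A simulation with 8 doses per child, within-child correlation 0.3 to 0.6 and stable facility effects gave 56% to 76% at 5 infants and 79% to 95% at 9. With a quarter of the facility variance unshared, it gave 76% to 82% even at 30.

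**The case against.** On Mozambique, the fair defence is that the article discloses the cancellation and that the power text is the original calculation made before the site moved. That explains the mismatch but does not remove it: the current text still claims power and children in each country. One could also suppose that only the baseline survey was dropped. The article provides for no later household survey in Mozambique. Even if one took place, an arm-by-survey interaction needs both surveys, and the end-line comparison has about 49% power on the printed inputs.

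On the other two countries the defence is stronger, and much of it stands. A reader might infer that the 80% is overstated there or cannot hold. The documents do not support that:
- The infant share is my assumption.
- The purpose of the reserve points is not stated, and they may replace households without an eligible child under a rule left to the full protocol. With all 90 points, most of the table's range is at or above 80%.
- Several doses per child can bring even 9 infants to 82%.
- The Outcomes prose gives no age limit, and Table 2 counts vaccines from the previous calendar year, so eligible children may be more numerous than infants on the survey day.

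A reader might also infer that facilities in Côte d'Ivoire have fewer than 30 households because villages fell short. The article does not say by how much, in how many catchment areas, or that the quota stayed at 10 per village.

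What remains is that no stated step in the sampling delivers an infant per household, so the assumption is unsupported rather than disproved.

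**Conclusion.** The point on Mozambique holds without any assumption: a primary outcome is declared powered in a country where its only stated data source has been cancelled. Power there is nil, and the household-based safeguard against measurement bias does not apply. This must be corrected.

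For Côte d'Ivoire and Nigeria the conclusion is narrower. The stated power depends on one child under 1 year in each randomly drawn household, and the article gives no basis for that. Under the assumed 15% to 30% share, the table runs from 30% power (4.5 infants, one observation per child, a tenth of facility variance unshared) to 82% from 30 households alone (9 infants, 10 doses, stable facility effects), and higher if the reserve points are used. The true figure may fall on either side of 80%, and the baseline surveys already hold the count that would settle the yield.

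**What to change.** 1. In Outcomes and Sample size calculations, limit vaccination adherence, its power and the 30 children per catchment area to Côte d'Ivoire and Nigeria.
2. List four primary outcomes for Mozambique, and say in Measures to minimise bias that the household-level safeguard does not apply there.
3. In Data analysis, state by country which primary outcomes are measured at both surveys. Satisfaction should be covered too, since that section ties its end-line-only measurement to Nigeria.
4. Limit conclusions on service coverage to the two surveyed countries.
5. For those two countries, replace the assumed 30 children per facility with the number of eligible children per facility found at baseline, rerun the existing simulation, and report the power whether it rises or falls. State what the reserve points were used for.

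Infant screening should not be introduced at end-line only. It would change the sampling between surveys under an arm-by-survey comparison, and it could distort under-5 mortality and client experience, which also use household samples. Villages sampled by the bottle method have no mapped reserve points to draw on.

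The cost is a few sentences, a count from data already collected and a rerun of existing code. The drawback is that the restated power may be less favourable.

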### Data collection and management

Data collection took place at baseline and will take place again at the end of the study. Data are collected from HFs, from the households in the catchment areas of the included HFs and also from district offices.

For data quality and data use outcomes, HF registers, tallies and reports will be scrutinised. For population-based outcomes, we carry out household surveys at baseline and at end-line. We use standard approaches for these types of surveys.^21^ Households are visited, the research project is briefly introduced and consent requested. Ideally, mothers of alive children or women in childbearing age is interviewed in order to obtain information on living children (ie, vaccination history) and death events, respectively, using home-based records if available and accessible. Patients’ satisfaction is assessed using the Patient Satisfaction Quaestionnaire (PSQ-18).^22^
^23^
^24^ Essentially, the tool enables practitioners to investigate the extent to which their healthcare service meets the perceived needs of their client group and pinpoint areas for improvement.^24^ The interview will be conducted with consenting individuals as close to their care encounter as possible.^25^ Data tools are translated into the official languages of the study countries and pilot tested for consistent meaning and relevance to the setting. Data collectors are also able to communicate in local languages. The Satisfaction of Employees in Health Care survey is a validated tool to assess staff satisfaction. It was first developed and validated in a low-income country (Ethiopia)^26^ and later successfully validated in a high-income country (USA).^27^

We use a mix of paper and electronic data (Open Data Kit (ODK)^28^) collection tools. Data collectors are trained to minimise error. Tools are piloted before implementing. ODK data are regularly stored and sent to secure servers, as soon as data collectors reach their office base. Data from paper tools are double entered and compared and sent to secure servers. Each data collection tool has its corresponding electronic database that is cleaned and submitted to the analyses. All data are anonymised at the point of data collection or as soon as possible in the data management process. Data are labelled with an arm code (eg, ‘A’ or ‘B’) without any further information allowing to disclose which data items belong to the intervention or to the control arms, ensuring blinding during data analyses.

Quality will be assured through several mechanisms: piloting of data collection tools; thorough training of field workers; checking missing data related; double, independent data entry from papers into digital databases; early descriptive analyses to detect potential outliers; fieldworkers tracking and supervision.

### Data analysis

The analysis will be carried out for each country separately, and based on intention to treat.

Baseline population and health facility characteristics (ie, basic demographic characteristics of population and HWs, professional profile of HWs, health facility size and services) will be summarised. If large imbalances are observed at baseline, the variables can be used to adjust the effect estimate comparisons.^29 30^

The analyses vary for the different primary outcomes due to the unit of measurement and levels of clustering, the type of variable, and whether measurements were taken at baseline and endpoint or endpoint only. We use regression models to allow us to estimate the effect of the outcome while flexibly accounting for these issues and allowing adjustment for potential confounders.

Logistic regression will be used for the binary variables: vaccine adherence is measured by determining whether each vaccine due was received, and treatment appropriateness by whether each treatment was correctly prescribed. Data concordance and diagnostic scope are count variables and may be analysed with Poisson regression, depending on their distribution. The regression model for HW satisfaction will depend on how it is distributed.

The outcomes have different levels of clustering (children or consultations, HW, HF). We will account for these levels of clustering by including random effects in the regression models.

Four of the primary outcomes are measured at baseline and end-line. The effect of the intervention will be estimated using an interaction term between arm and survey in the regression models: that is, is the change in the outcome between baseline and follow-up in the intervention arm different to the change between baseline and follow-up in the control arm? The effect of HW satisfaction in Nigeria, measured only at end-line, will be estimated as the difference between the intervention and control arms.

All estimates for the effect of the intervention will be presented with 95% CIs. The analyses will be carried out using R.^31^

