### Outcomes

There are five primary outcomes (table 2). Vaccination adherence is defined as the total number of vaccine doses given in the correct time interval to children in households in the HFs catchment villages over the total number of vaccine doses that should have been given during the same period. Antenatal care visits uptake will also be considered depending on the expected number of pregnancies in the study areas. Both are used as proxies for health outcomes in terms of protection against disease^13^ and prevention of pregnancy complications^14^ and are assessed in a random sample of households in the HFs catchment areas. Data concordance is defined as the level of agreement of HIS indicators between (1) records of healthcare events (recounts), (2) tallies (recounts) and (3) reports (aggregated data to higher levels of the system).^3^ Decision making will be assessed considering the diagnostics scope in the sick child (ie, number of different diagnoses per sick child consultation) and treatment appropriateness (ie, number of prescribed treatments that are supported by a documented diagnosis). These outcomes will be assessed in a random sample of records and corresponding reports during the last 4 months of the study period. HWs satisfaction will be assessed in all HWs in included HFs using a standardised questionnaire.^15–17^ While the intervention targets HF, some of the outcomes are measured at the level of HF and some others in the communities of HF catchment areas.

**Table 2 T2:** Outcomes and parameters used to estimate the sample sizes

	Outcome name	Subjects	Definition	Baseline estimate	Expected change	Comments
1	Vaccination adherence	Children under 1 year (sample of households in catchment areas)	Number of vaccines given in the previous calendar year over the number of vaccine due in the same period	75 given per 100 due	Increase of 10 per 100	Vaccines are clustered within children, and children within HFs
2	Data concordance	Recording tools in health facilities (samples of records)	Number of healthcare events (eg, vaccinations, antenatal care consultations) recounted in the previous calendar year vs the number of healthcare events reported in the same time period	Seven recounted for each 10 reported^3^	Increase of 1 recounted	A single estimate can be obtained in each HF or by time periods (no clustering)

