3	Diagnostic scope	Records of sick child consultations (samples of records)	Number of diagnosis in each sick child consultation during the previous calendar year	30% with more than one diagnosis	35% with more than one diagnosis	Individual consultations are clustered within HF
4	Treatment appropriateness	Records of sick child consultations (samples of records)	Number of treatments correctly prescribed in each sick child consultation during the previous calendar year	Half appropriate over all consultations	Increase to 60%	Individual consultations are clustered within HF (one treatment per child)
5	Health workforce satisfaction	Health workers (all health workers form include health facilities)	Degree (score) of satisfaction with the HIS across all health facilities in each arm	50% satisfied	75% satisfied	More than one health workers can be approached in each HF

HF, health facility; HIS, Health Information System.

Secondary outcomes are classified under the following domains: data quality, data use, mortality, HW experience, client experience and resource consumption:

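### Diagnostic scope is defined and listed for analysis as a count, but its effect size and power are stated as a proportion, and that proportion does not fix the power of a count analysis

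*Protocol article*

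**What the plan says.** **Definition.** The Outcomes text describes diagnostic scope as the "number of different diagnoses per sick child consultation", and Table 2 gives the same thing: "Number of diagnosis in each sick child consultation during the previous calendar year". Both are counts.

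**Effect and power.** In the same row of Table 2 the baseline is "30% with more than one diagnosis" and the expected value is "35% with more than one diagnosis". The sample size section says the trial could "detect an increase in the proportion of child visits with more than one diagnosis from 30% to 35% with 80% power". The inputs named for this calculation are "35 HF per arm, 60 records per HF and assuming a k of 0.25". These are statements about a binary variable.

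**Analysis.** The Data analysis section assigns logistic regression to vaccine adherence and treatment appropriateness. Diagnostic scope is not in that group: "Data concordance and diagnostic scope are count variables and may be analysed with Poisson regression, depending on their distribution". Clustering is handled by random effects. The effect is the arm-by-survey interaction for the four outcomes measured at both surveys. The sample size section adds that the simulated trials were analysed with the models of the analysis section.

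**The concern.** A rise from 30% to 35% above one diagnosis fits many different changes in the mean number of diagnoses. It depends on how many consultations have none, and on how many have three or more. So the stated power does not transfer to a count analysis unless the count distribution is given, and it is not.

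The choice of model also matters. A Poisson model sets the variance equal to the mean. If most sick child consultations have at least one recorded diagnosis and few have more than two, the variance is far below the mean. Random effects add variance, so they cannot correct this. The standard error is then too large and the interval too wide, and a real 30% to 35% effect could easily be missed in each country's separate analysis.

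**Working it through.** **Inputs from the article.** 35 facilities per arm and 60 records per facility, so N = 35 × 60 = 2,100 records per arm and survey; k = 0.25; 30% and 35% above one diagnosis; type I error 0.05 (sidedness not stated); effect = arm-by-survey interaction. I take the facility effect as constant across the two surveys.

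**Step 1: the plan's 80%.**

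*Binary interaction.* SE = √[(3 × 0.30 × 0.70 + 0.35 × 0.65)/2100] = √(0.8575/2100) = 0.0202. Then 0.05/0.0202 = 2.474. Two-sided power = Φ(2.474 − 1.96) = 0.70 (simulated 0.69). One-sided power = Φ(2.474 − 1.645) = 0.80. An end-line-only comparison by the Hayes and Bennett formula gives 0.53 to 0.54 two-sided.

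*True Poisson counts.* Solve 1 − e^(−λ)(1 + λ) = 0.30 and 0.35. This gives λ = 1.097 and 1.235. The log rate ratio is 0.1182. SE = √[(3/1.097 + 1/1.235)/2100] = 0.0411. Two-sided power = Φ(0.1182/0.0411 − 1.96) = 0.82 (simulated with k = 0.25: 0.816). This form implies e^(−1.097) = 33% of consultations with no diagnosis, falling to e^(−1.235) = 29%.

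So about 80% is recovered by a one-sided binary test or by truly Poisson counts, but not by a two-sided test of the proportion.

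**Step 2: plain Poisson applied to other count shapes.** All have 30% and 35% above one. With means μ0, μ1 and variances v0, v1:

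- model SE = √[(3/μ0 + 1/μ1)/N]
- true SE = √[(3v0/μ0² + v1/μ1²)/N]
- power = Φ[(ln(μ1/μ0) − 1.96 × model SE)/true SE]

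For one or two diagnoses only: μ = 1.30 and 1.35, v = 0.21 and 0.2275. Model SE = 0.0381, true SE = 0.0154, ratio 2.48. Power = Φ[(0.0377 − 0.0747)/0.0154] = 0.8% (simulated 0.7%).

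| Assumed shape | Model SE / true SE | Poisson power |
|---|---|---|
| All 1 or 2 | 2.48 | 0.8% |
| At least 1; 8% with three at baseline, rising in proportion | 1.86 | 8% |
| 10% none, unchanged; maximum 2 | 1.82 | 5% |
| 20% none, unchanged; maximum 2 | 1.49 | 9% |
| 30% none, unchanged; maximum 2 | 1.29 | 14% |
| 20% none falling to 15%; maximum 2 | 1.52 | 59% |
| True Poisson (33% none falling to 29%) | 1.00 | 82% |

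The 59% row has means 1.10 and 1.20, model SE 0.0412 and true SE 0.0270: Φ[(0.0870 − 0.0807)/0.0270] = Φ(0.23).

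**The case against.** The strongest reply is that the article does not commit to Poisson. It says the model may be used, depending on the distribution, and variance far below the mean is exactly what an analyst looking at the distribution would see. A reader might infer that the plan will report a real effect as null. The text does not support that: it requires plain Poisson to be kept despite gross misfit.

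A second tempting reading is that the count is strongly under-dispersed as a matter of fact. The article gives only the share above one. Consultations without a documented diagnosis are plausible: the treatment outcome counts treatments supported by a documented diagnosis and assumes half are appropriate at baseline, and the new tools add space to document diagnoses. So the factor of 2.5 is one end of a range.

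A third is that the simulation must have used a different endpoint from the analysis. That is not established either. True Poisson counts with 30% and 35% above one give 82%, close to the stated 80%. The simulation code is in supplements that are not shown.

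It is also fair that fallback models are commonly left to the analysis plan, that model choice is made blind to arm identity, and that the error is conservative. All of this limits the severity. It does not remove the mismatch, because the article itself states both forms and does not link them.

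**Conclusion.** The point holds as a mismatch between the form in which diagnostic scope is powered and the form in which it is defined and listed for analysis. The stated 80% is valid for a two-sided Poisson count analysis only under a distribution that the article does not state. Under every non-Poisson shape tried, plain Poisson intervals are too wide, by 1.3 to 2.5 times, and power lies between about 1% and 59%. The top of the ratio range and the bottom of the power range rest on the assumption that every consultation has exactly one or two diagnoses.

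These figures assume 60 records per facility at each survey, a two-sided test and a facility effect that persists between surveys. If that effect were independent between surveys, the binary interaction power would fall to about 32%.

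The matter affects one of five primary outcomes and does not inflate type I error. It should be fixed, but a null result is not a foregone conclusion.

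**What to change.** State one form of the endpoint and use it in the Outcomes text, Table 2, the sample size section and the Data analysis section. Either option works.

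1. **Binary.** Define diagnostic scope as more than one diagnosis recorded, yes or no. Analyse it with the mixed logistic arm-by-survey interaction already planned for the other binary outcomes. Restate the power: about 70% two-sided under the stated inputs, below the 80% that the article requires. Report the mean number of diagnoses descriptively.

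2. **Count.** Keep the number of diagnoses and state its assumed distribution, including the share with none in each arm. Use a variance estimate that allows under-dispersion, for example robust and clustered on health facility, and give power for that analysis. This option does not guarantee 80% either: with a correct SE, Φ(ln(μ1/μ0)/true SE − 1.96) is 69% for the one-or-two shape and 30% to 47% when 10% to 30% have none and that share does not change.

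The same records serve both options, so no new data are needed. The cost is a change of wording and a rerun of the power simulation, with sidedness stated. The choice should be recorded before the arms are disclosed to the analysts.
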